**Figure 1 fig1:**
[figure not shown]
Study flowchart.

Ethical approval has been granted by the Clinical Research Ethics Committee of China-Japan Friendship Hospital (Approval No. 2025-KY-125-1). Any amendments to the trial protocol require submission to and re-approval by the Committee prior to implementation, and will be updated in the trial registry in a timely manner. This study is a joint research project sponsored by the China Association of Chinese Medicine and funded by Guangdong Efong Pharmaceutical Co., Ltd. Notably, the funder will not be involved in the study design, data collection and management, or data analysis. Participant recruitment for this trial is ongoing, and written informed consent has been obtained from all participants. The trial will be reported in compliance with the CONSORT guidelines and has been registered with the International Traditional Medicine Clinical Trial Registry (Identifier: ITMCTR2025001210; available at: https://itmctr.ccebtcm.org.cn/mgt/project/view/2038531670868623360). The detailed schedule for interventions and assessments is provided in Table 1.

**Table 1 tab1:** Study schedule.

Items	Screening (day −3 to Day 0)	Baseline (day 0)	Visit 1 (day 7 ± 1)	Visit 2 (day 14 ± 1)	Telephone follow-up (day 21 ± 1)
Written informed consent	√				
Collection of demographic data	√				
Medical history (past 3 months)	√				
Concomitant diseases and symptoms	√				
Vital signs	√		√	√	
Pulmonary auscultation	√		√	√	
Concomitant medications	√	√	√	√	√
CSS	√		Based on diary card records		√
CET	√		√	√	
TCM syndrome score	√		√	√	
LCQ	√			√	
Complete blood count	√			√	
Urinalysis	√			√	
Liver and renal Function tests	√			√	
12-Lead Electrocardiogram	√			√	
Chest X-ray or chest CT	√				
Pulmonary function test (including bronchodilator test)	√				
Serum pregnancy test (women of childbearing age)	√			√	
Adverse event recording		√	√	√	√
Randomization		√			
Dispensation of study medication		√			
Dispensation of diary card		√			
Return of study medication				√	
Return of diary card				√	
Compliance assessment			√	√	

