### Participants

2.3

In this trial, PIC is defined according to the following criteria: (1) History of infection: A history of respiratory tract infection prior to the onset of cough. (2) Clinical manifestations: Presence of an irritant dry cough or a small amount of white, viscous sputum. (3) Duration: Cough typically persists for a period of 3 to 8 weeks. (4) Imaging findings: No significant abnormalities detected on chest X-ray or CT scan. (5) Differential diagnosis: Exclusion of cough caused by other underlying etiologies (e.g., cough-variant asthma, upper airway cough syndrome, or gastroesophageal reflux-induced cough).

The detailed diagnostic criteria for the Wind invasion-Dampness obstruction syndrome are provided in Table 2. The Cough Symptom Score (CSS) is divided into two components: daytime and nighttime scores. Based on the intensity and frequency of the cough, as well as the degree of its impact on the patient’s sleep and daily activities, the symptoms are categorized into four grades, scored from 0 to 3. The total CSS is defined as the sum of the daytime and nighttime scores (Table 3).

**Table 2 tab2:** Diagnostic criteria for Wind invasion-Dampness obstruction syndrome.

Category	Symptoms and signs
Primary symptoms	① Cough ② Throat itching or discomfort ③ Sudden onset or exacerbation triggered by temperature changes (cold or heat), irritant odors, or similar factors
Secondary symptoms	① Sticky sensation in the mouth ② Loss of appetite ③ Abdominal distension
Tongue signs	Pale tongue with white moist or white greasy coating
Pulse signs	Floating pulse, floating-moderate pulse, floating-soft pulse, floating-slippery pulse, floating-thin pulse, or normal pulse

The syndrome is diagnosed when the primary symptom is present, ≥2 secondary symptoms are met, together with corresponding tongue and pulse signs.

**Table 3 tab3:** Cough symptom score.

Daytime	Nighttime
□0 points: No cough	□0 points: No cough
□1 point: Occasional brief cough	□1 point: Brief cough at sleep onset or occasional nocturnal cough
□2 points: Frequent cough, mildly affecting daily activities	□2 points: Cough mildly affecting nighttime sleep
□3 points: Frequent cough, severely affecting daily activities	□3 points: Cough severely affecting nighttime sleep

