#### Primary outcome

2.6.1

The primary outcome measure is the cough relief rate after 14 days of treatment. Cough relief is defined as a total CSS (daytime + nighttime) ≤ 2, sustained for at least 48 h ± 2 h. Cough cure is defined as a total CSS (daytime + nighttime) ≤ 1, sustained for at least 48 h ± 2 h. The CSS will be recorded at baseline and daily throughout the study. The inter-group difference in the 14-day cough relief rate will be evaluated according to these diagnostic criteria.

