(5) Cough Cure and Relief Rates: Based on daily CSS records and predefined criteria, the inter-group differences in the cough cure rate (at day 7 and day 14) and the cough relief rate (at day 7) will be evaluated.(6) Time to Cough Cure and Relief: Based on daily CSS records, the inter-group differences in the median time to reach cough cure and relief within the 14-day period will be analyzed.(7) Cough Recurrence Rate: This is defined as the proportion of participants who achieved relief by the end of treatment but experienced a recurrence of cough during the 7-day post-treatment follow-up.

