Based on the theory of “Wind Cough,” our research group proposed the “Wind invasion-Dampness obstruction” syndrome. By modifying the Suhuang Zhike decoction with additional dampness-resolving herbs, we developed the SFHS formula (26). *Ephedrae Herba* (Mahuang) serves as the monarch herb to disperse pathogenic factors in the lung, thereby relieving cough and asthma. *Armeniacae Semen Amarum* (Kuxingren) and *Stemonae Radix* (Baibu) act as minister herbs to suppress cough and resolve phlegm, while *Atractylodis Rhizoma* (Cangzhu) and *Magnoliae Officinalis Cortex* (Houpo) strengthen the spleen and eliminate dampness. *Perillae Fructus* (Zisuzi) and *Peucedani Radix* (Qianhu) are used as adjuvant herbs, which not only enhance the wind-dispelling effect of Mahuang but also promote the coordination of ascending and descending Lung qi. *Cicadae Periostracum* (Chantui), as the courier herb, further disperses wind pathogens and helps relieve throat itching. Since 2022, this formula has been used as an institutional formula in our hospital, with over 12,000 doses administered. This study aims to evaluate the efficacy and safety of the SFHS formula in alleviating clinical symptoms and reducing the recurrence rate of PIC.

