The study employs a 2:1 allocation ratio (treatment vs. control) to minimize the exposure of participants to negative interventions (placebo), thereby enhancing recruitment feasibility and meeting ethical considerations. Regarding treatment duration, a review (unpublished data) of published RCTs on PIC conducted by our research team indicated that study durations predominantly range from 7 to 14 days. Accordingly, a 14-day continuous treatment period was selected, with assessments scheduled at days 7 and 14. This duration was considered sufficient to ensure adequate drug exposure for efficacy evaluation, while avoiding an excessively prolonged course that might compromise participant adherence. The day-7 visit additionally allows for assessment of early treatment response. To precisely evaluate the dynamic changes in cough severity and its impact on daily life, the cough relief rate was established as the primary outcome measure. Furthermore, a multidimensional evaluation framework—incorporating the CSS, CET, and LCQ—was implemented to overcome the inherent limitations of any single scoring system. From the perspective of TCM pattern identification and holism, the TCM Syndrome Score is utilized to assess the specific advantages of the SFHS formula in systemic symptom improvement. Finally, a one-week post-treatment follow-up was integrated to monitor symptom fluctuations and assess the recurrence rate after drug withdrawal, providing a comprehensive view of the treatment’s sustained efficacy.

This study has several strengths. First, the multicenter design enables recruitment of a broader and more diverse participant population, thereby reducing the selection bias associated with single-center studies and enhancing the generalizability of the findings. Second, the use of multiple cough assessment scales as outcome measures overcomes the limitations of any single tool and provides a multidimensional evaluation of subjective cough symptoms. Finally, to evaluate the durability of the therapeutic effect of SFHS, a one-week post-treatment follow-up period was incorporated (27, 28), informed by limitations identified in prior studies recommending surveillance of cough recurrence following treatment withdrawal (23, 24). This follow-up period allows for monitoring of symptom recurrence after treatment cessation and assessment of the sustained nature of the clinical response.

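### Cough recurrence is defined over the whole week after treatment, but the schedule takes the diary back at Visit 2 and leaves one telephone CSS at day 21

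*Protocol article*

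**What the plan says.** Section 2.6.2, item (7), counts participants who "achieved relief by the end of treatment but experienced a recurrence of cough during the 7-day post-treatment follow-up". Relief itself (section 2.6.1) is a total CSS of 2 or less held for about 48 hours. The recurrence item gives no CSS value and no duration.

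On data capture, section 2.6.1 states: "The CSS will be recorded at baseline and daily throughout the study". Table 1 is different. On treatment, the CSS row reads "Based on diary card records". The row "Return of diary card" is ticked at Visit 2 (day 14 ± 1), a diary is dispensed only at baseline, and the only contact after Visit 2 is the day 21 ± 1 telephone call, with one CSS tick.

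The Discussion says the follow-up week is there "to monitor symptom fluctuations and assess the recurrence rate after drug withdrawal", and it lists that week among the trial's strengths. The limitations paragraph concedes that the follow-up is short, but not that it rests on a single scheduled score.

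**The concern.** The outcome is defined over an interval, while the schedule supplies an observation at one point. If sites follow Table 1, there is no daily record for days 15 to 20, and no later analysis plan can recover data that were never collected. A participant relieved on day 14 who scores 4 on days 16 to 18 and is back at 2 on day 21 need not appear as a recurrence.

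At stake is the evidence on durability. A recurrence rate drawn from the single score would tend to be too low in both arms. It would describe status on one day, although its label covers a week. The stated aim of following symptom fluctuation after withdrawal could not be met.

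**Working it through.** **Plan's own figures.** The protocol article gives no number for recurrence. Its sample size for the primary endpoint does reproduce: (1.960 + 1.282)² × (0.48×0.52 + 0.88×0.12/2) / (0.40 − 0.10)² = 35.3, so 36 control participants, and twice 35.3 = 70.6, so 71 treated. It has no bearing on this point.

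**Coverage by schedule.**
- Period named in item (7): seven days, 15 to 21.
- CSS under section 2.6.1: daily.
- CSS under Table 1: none on days 15 to 20, one at about day 21.

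Section 2.6.1 and Table 1 cannot both be followed after day 14.

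**Share of episodes seen.** These are assumptions, not document figures: the call records the current day's score only; each recurrence is one episode of d days; its first day is equally likely to be any of the L days up to and including the call. The episode is seen only if it starts within the last d days, so

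P(detected) = min(d, L) / L.

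Nominally L = 21 − 14 = 7. The visit windows allow L from 20 − 15 = 5 to 22 − 13 = 9.

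| Episode length | L = 5 | L = 7 | L = 9 |
|---|---|---|---|
| 2 days | 40% | 2/7 = 29% | 22% |
| 3 days | 60% | 3/7 = 43% | 33% |
| 5 days | 100% | 5/7 = 71% | 56% |
| Lasts to the call | 100% | 100% | 100% |

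**Effect on a comparison (illustration only).** At the planning rates, the responders number about 80 × 0.88 = 70 and 40 × 0.48 = 19. Suppose true recurrence is 20% on SFHS and 40% on placebo, and all episodes last 2 days. The call would then show 0.20 × 2/7 = 5.7% and 0.40 × 2/7 = 11.4%. The difference falls from 20 to 5.7 percentage points, while the ratio stays at 0.5. Normal-approximation power (pooled variance under the null, two-sided 0.05) falls from about 44% to about 18%. The second figure is rough, because only about 70 × 0.057 = 4 and 19 × 0.114 = 2 events would be expected.

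**The case against.** The strongest reply is that nothing in the document limits the call to that day's score. Item (7) speaks of the whole week, and the same call also collects adverse events and concomitant medication, which are normally asked about since the last contact. A seven-day recall is neither stated nor excluded. This stands, and it makes the detection shares conditional. A reader might infer that most short recurrences will be missed; that follows only for a current-day score and episodes of about three days or less. Unstructured recall would still fall short of the daily record that section 2.6.1 promises.

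A reader might also infer that durability cannot be assessed at all. The document does not support that. Status one week after stopping, in participants relieved at day 14, bears directly on sustained response. It is collected in the same way in both blinded arms, and if episode lengths are similar the relative effect is preserved.

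A third tempting inference is that PIC cannot recur in seven days, because the Discussion aims at "alleviating clinical symptoms and reducing the recurrence rate of PIC" while section 2.3 says "Cough typically persists for a period of 3 to 8 weeks". This is weak. The criterion describes what is typical, participants have already met it at entry, and cough that returns after withdrawal can belong to the same episode. Item (7) is named for cough, and the limitations paragraph already says longer observation is needed to track recurrence after later infections.

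Finally, a CSS cut-off for a secondary outcome may well sit in the full protocol or SAP, and loss of relief is its natural reading. The missing cut-off is therefore a subsidiary matter. The missing daily record is not, because it is a question of data collection.

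**Conclusion.** The point holds as a mismatch between an outcome defined over seven days and a schedule with one CSS after the diary is returned, together with a direct conflict between section 2.6.1 and Table 1 on CSS capture after day 14. Relapses that resolve before the call can be missed; relapse present at the call is not. Over a nominal seven-day gap the call would see 29%, 43% and 71% of 2-, 3- and 5-day episodes, provided that it records the current day only and onset is uniform. The protocol fixes neither condition, nor does it give any episode length. The absolute recurrence rate, the power of the comparison and the description of fluctuation are weakened; the durability question as a whole is not lost. It is worth correcting while recruitment continues.

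**What to change.** Reconcile section 2.6.1 with Table 1 by keeping the CSS diary through day 21, either on the same card or on a second card dispensed at Visit 2, with the daily scores read out at the call.

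Define recurrence as loss of the relief criterion among Day 14 responders: total CSS of 3 or more, with a stated duration rule (the 48-hour rule used for relief is an obvious model). Say how an episode that starts too close to day 21 to be confirmed will be counted. State what period the telephone CSS covers.

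For participants already past day 14, only the single score will exist. Keep day-21 status as the common measure for everyone, and report diary-based recurrence for those followed under the amendment.

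If the diary is not extended, rename the outcome *relapse status at day 21* and drop the claim to monitor fluctuation.

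The cost is seven more diary days per participant, return of the card by post or photograph, an amendment with ethics approval and a registry update, and mixed ascertainment between participants enrolled before and after the change. No extra visit is needed.

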#### Other outcomes

2.6.3

Routine laboratory assessments, including complete blood count (CBC), urinalysis, liver and renal function tests, and 12-lead electrocardiography (ECG), will be performed at baseline and on day 14 to monitor safety. Additionally, women of childbearing potential will undergo serum pregnancy tests at baseline and on day 14 to ensure the absence of pregnancy-related risks throughout the study period.

### Sample size calculation

2.7

The sample size was estimated based on efficacy data from previous clinical trials. The cough relief rate for Suhuang Zhike Capsule was reported to be 87.75–93.33% (8, 14); thus, the expected relief rate for the Shufeng Huashi formula (π_T_) was estimated at 88%. The relief rate for the placebo, based on previous studies, ranged from 47.76–58.51% (15, 16); therefore, the expected relief rate for the placebo group (π_C_) was set at 48%. A 2:1 superiority design was employed, with a two-sided significance level of *α* = 0.05 and a power of 0.9 (1 − *β* = 0.9). A clinical superiority margin of 10% was considered. Using PASS 21 software for sample size estimation, the calculated requirement was 71 participants for the treatment group and 36 for the control group. Accounting for a 10% dropout rate and potential unforeseen data loss during trial execution, a total of 120 participants will be enrolled, with 80 in the treatment group and 40 in the control group. Participants will be recruited through outpatient clinics and advertisements.

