### Study design

2.1

A randomized, double-blind, placebo-controlled, parallel-group, superiority clinical trial design will be employed. The study will be conducted across six hospitals in three regions of China: China-Japan Friendship Hospital (Beijing), the Third Affiliated Hospital of Beijing University of Chinese Medicine (Beijing), Wangjing Hospital of the China Academy of Chinese Medical Sciences (Beijing), Huairou Hospital of Beijing Traditional Chinese Medicine Hospital (Beijing), Wuqing District People’s Hospital (Tianjin), and the Affiliated Traditional Chinese Medicine Hospital of Southwest Medical University (Sichuan). Trial monitoring will be conducted on-site, with each study center receiving an initiation visit, a close-out visit, and two routine monitoring visits.

The overall study period spans from November 2024 to November 2027. The initial phase (November 2024 to October 2025) was devoted to protocol development and trial preparation, with no participant enrollment or screening conducted prior to the receipt of ethical approval and trial registration. Participant recruitment and intervention are scheduled between November 4, 2025, and November 30, 2027. The detailed study flow is illustrated in Figure 1. This protocol adheres to the SPIRIT 2025 guidelines and is conducted in accordance with the ethical principles outlined in the Declaration of Helsinki.

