### Statistical analysis

2.10

Statistical analyses will be performed using SAS version 9.4 or a higher version.

The analysis populations are defined as follows: the Full Analysis Set (FAS) includes all randomized subjects who receive at least one administration of the investigational drug; the Per Protocol Set (PPS) includes all subjects in the FAS who comply with the study protocol, demonstrate good compliance, have complete primary efficacy endpoint data, do not use concomitant medications affecting efficacy evaluation, and have no major protocol deviations; the Safety Set (SS) includes all subjects who receive at least one administration of the study drug after randomization and have safety assessment data, and will be used as the safety analysis population.

Primary efficacy endpoint analysis: the primary endpoint is the cough relief rate on Day 14, defined as the proportion of subjects with a CSS total score ≤2 at the Day 14 visit and maintained for 48 h ± 2 h. Regardless of whether subjects experience transient relief during the treatment period, the final determination will be based on the CSS status at the Day 14 visit. This endpoint is a binary outcome and will be analyzed using the Cochran–Mantel–Haenszel (CMH) χ^2^ test stratified by center as the primary analysis model, separately in the FAS and PPS populations. Differences in relief rates between groups will be estimated using risk difference (RD), with point estimates, corresponding two-sided 95% confidence intervals, and *p* values reported. In addition, supplementary Logistic regression analyses will be performed with treatment group, center, and baseline CSS score as covariates to assess the robustness of the primary conclusions after covariate adjustment. For missing data of the primary endpoint, the Last Observation Carried Forward (LOCF) method will be used as the primary handling approach. To evaluate the robustness of the primary conclusions under assumptions regarding missing data, multiple imputation (MI) sensitivity analyses will be conducted under the Missing At Random (MAR) assumption, using baseline CSS score, treatment group, center, and all available post-baseline observations as imputation variables to impute missing values. The results obtained from both methods will be reported and compared simultaneously.

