Secondary efficacy endpoint analysis: for quantitative variables, descriptive statistics will include number of cases (*n*), mean, standard deviation (SD), minimum, maximum, median, lower quartile (Q1), upper quartile (Q3), and 95% confidence interval (95%CI). Prior to analysis, normality tests will be performed for variable distributions: if the data conform to a normal distribution, inter-group comparisons will be conducted using the independent-samples *t* test, and within-group pre- and post-treatment comparisons will be conducted using the paired *t* test; if the data do not conform to a normal distribution, inter-group comparisons will be conducted using the Wilcoxon rank-sum test, and within-group pre- and post-treatment comparisons will be conducted using the Wilcoxon signed-rank test. For categorical variables, results will be described using frequencies and percentages. When considering the impact of center effects, binary and ordinal variables will be analyzed using the CMH χ^2^ test, and 95% confidence intervals for between-group risk differences will be provided for binary variables; when adjustment for baseline imbalance or other covariates is required, Logistic regression analysis will be used. For time-to-event variables, median time, lower and upper quartiles, and 95% confidence intervals will be described, Kaplan–Meier survival curves will be plotted, and inter-group comparisons will be performed using the log-rank test.

All statistical tests will be two-sided, and *p* < 0.05 will be considered statistically significant.

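### The sample size assumes a 10-point superiority margin, but the stated primary test is against a zero difference, so the quoted 90% power belongs to a different test and the margin has no decision rule

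*Protocol article*

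**What the plan says.** Section 2.1 describes the trial only in general terms: "A randomized, double-blind, placebo-controlled, parallel-group, superiority clinical trial design will be employed". Section 2.7 gives the design inputs: relief rates of 88% on SFHS and 48% on placebo, two-sided alpha of 0.05, power of 0.9, and "A 2:1 superiority design was employed". It then adds: "A clinical superiority margin of 10% was considered". The stated requirement is 71 plus 36, raised to 80 plus 40 for dropout.

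Section 2.10 makes the primary analysis a CMH chi-square test "stratified by center as the primary analysis model, separately in the FAS and PPS populations". It also asks for the risk difference with a two-sided 95% confidence interval and a p value. The only threshold it gives is that two-sided p < 0.05 "will be considered statistically significant". The 10% margin appears nowhere outside 2.7. There is no shifted null, no rule comparing a confidence limit with 10 points, and no remark that the margin served planning only.

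**The concern.** A sample size calculation with a superiority margin has as its null that the difference is at most 10 points. A CMH test has as its null that there is no association, that is, a zero difference. These are two hypotheses with two different success bars, and the article states the first for sizing and the second for analysis.

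Two things are at stake. First, the power statement does not describe the test that will be run. Second, a range of results would be significant under 2.10 yet fall short of the margin in 2.7, and nothing says how such a result is to be read. If that is settled only after unblinding, the choice is post hoc.

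The range is not remote. The 88% is borrowed from a related product (Suhuang Zhike Capsule), and the 48% sits at the bottom of the placebo range that 2.7 cites (47.76–58.51%). A true difference below 40 points is plausible, and that is where the two rules diverge.

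**Working it through.** **Inputs (all from 2.7):** π_T = 0.88, π_C = 0.48, allocation 2:1, two-sided α = 0.05 (z = 1.960), power 0.90 (z = 1.282), margin δ = 0.10.

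**Step 1. Reproduce the stated size.** With unpooled variance,

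n_C = (1.960 + 1.282)² × [π_T(1 − π_T)/2 + π_C(1 − π_C)] / (π_T − π_C − δ)²

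The variance term is 0.88 × 0.12/2 + 0.48 × 0.52 = 0.0528 + 0.2496 = 0.3024, and the squared z sum is 10.507.

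| Margin | Denominator | n_C | n_T = 2 n_C | Rounded up |
|---|---|---|---|---|
| 10 points | 0.30² = 0.09 | 35.30 | 70.61 | 36 and 71 (as stated) |
| none | 0.40² = 0.16 | 19.86 | 39.72 | 20 and 40 |

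Continuity correction of the no-margin calculation gives 23 and 46, still far from 36 and 71. Dropout is consistent: 107/0.90 = 118.9, so 119, against 120 enrolled.

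**Step 2. Power of each test at the design rates** (normal approximation, unpooled). At 71/36 the standard error is √(0.1056/71 + 0.2496/36) = 0.0918.

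- Margin test: Φ(0.30/0.0918 − 1.960) = 90.5%; at 80/40, 93.2%.
- Zero-difference test: Φ(0.40/0.0918 − 1.960) = 99.2% (99.3% with pooled variance under the null); at 80/40, 99.6% (99.7% pooled).

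**Step 3. Observed difference needed.** Take 80/40 analysed, with 19/40 placebo responders (47.5%):

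| SFHS responders | Difference | 95% CI (Wald) | Above 0 | Above 10 points |
|---|---|---|---|---|
| 52/80 | 17.5 | −1.2 to 36.2 | no | no |
| 53/80 | 18.75 | 0.1 to 37.4 | yes | no |
| 60/80 | 27.5 | 9.3 to 45.7 | yes | no |
| 61/80 | 28.75 | 10.7 to 46.8 | yes | yes |

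The pooled chi-square test also becomes significant at 53/80 (p = 0.048). So 53 to 60 SFHS responders would be significant under 2.10 without meeting the margin.

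**Step 4. How often the rules reject in favour of SFHS when the true difference is exactly 10 points** (exact binomial enumeration, 80/40, unstratified, placebo rates spanning the range in 2.7):

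| True rates | Zero-difference test | Margin test |
|---|---|---|
| 58% vs 48% | 17% | 3% |
| 68.5% vs 58.5% | 19% | 3% |

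With no true difference (48% vs 48%), the zero-difference test favours SFHS in 2.3% of trials, so its error rate is as intended. At an illustrative 70% vs 48% with 71/36 (normal approximation), the two rules succeed in about 60% and 23% of trials.

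**The case against.** The strongest reply is that the stated test is valid. A CMH test at two-sided 0.05 controls type I error for the conventional superiority null in a placebo-controlled trial, and 2.1 promises no more than superiority. The mismatch also runs in the safe direction, because the trial is larger than that test needs. All of this stands.

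A reader might infer from the 17–19% in step 4 that the false-positive rate is inflated. It is not: when the true difference is 10 points, rejecting a zero difference is correct. The figures show only how far apart the two rules lie.

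A reader might also infer that the trial will claim superiority by its margin on p < 0.05 alone. The text does not say so. Section 2.10 ties p < 0.05 only to statistical significance, and the wording in 2.7 is compatible with a conservative planning device. Which hypothesis the sponsor intends is not settled by the document.

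It can further be said that the planned 95% confidence interval lets anyone check the margin, and that a statistical analysis plan, not shown, may hold the rule. The interval does help, but no conclusion is attached to it. Nor is this merely an omitted detail, because the article states a test and a significance threshold that do not match its own sizing hypothesis.

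That the primary analysis is run in both FAS and PPS is a separate matter, commonly left to the analysis plan, and carries no weight here.

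**Conclusion.** The inconsistency between 2.7 and 2.10 is real and needs correction. The stated 71/36 needs the 10-point margin (107 evaluable against about 60 without it), while the stated primary test ignores it. The quoted 90% is the power of the margin test; the test in 2.10 has about 99%. The margin hypothesis has no decision rule. With 80/40 and placebo relief near 48%, the two rules disagree for observed differences from about 19 to just under 29 points.

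This is not a finding of an invalid or underpowered test. The figures take the relief rates in 2.7 at face value and ignore centre stratification. The true rates of 58%, 68.5% and 70% on SFHS are illustrative assumptions.

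**What to change.** Reconcile the two sections before unblinding, by one of two routes.

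(a) **Test the margin.** State in 2.10 that superiority is concluded only if the lower limit of the two-sided 95% confidence interval for the centre-stratified risk difference exceeds 10 percentage points, and report the CMH p value as the test of any difference. The sample size is unchanged and power is about 90% at 71/36. The cost is a higher success bar: about 29 observed points instead of about 19 in the example above.

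(b) **Test zero.** State that the primary hypothesis is a zero difference, and remove the margin from 2.7 or label it a conservative planning device. Restate the power of 71/36 as about 99%. Make no claim of superiority by the margin unless the lower confidence limit exceeds 10 points. The cost is giving up the margin as a criterion of success.

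Either route takes a few sentences and no extra participants. Recruitment is ongoing, so the change would go through the ethics committee and registry update that the article already prescribes for amendments.
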